### Data Analysis: Data Encoding

A data matrix will be created, and data will be processed statistically using SPSS, version 22 (IBM). Statistical significance will be set at 95% (α=.05).

A uni-bivariate descriptive analysis will be performed to determine the sample distribution for each of the variables studied, both for the total sample and for each group. The characterization variables will be summarized using descriptive statistics, expressing qualitative variables in terms of frequency and percentages and quantitative variables in terms of mean and SD.

Before the analysis, the normality of the variables will be evaluated using the Kolmogorov-Smirnov and Shapiro-Wilk tests. Baseline differences in the variables related to the sample profile between the intervention and control groups will be compared using the Student *t* test when these are normally distributed and the nonparametric Mann-Whitney *U* test in case they are not. Differences between dichotomous qualitative variables will be established using the chi-square test or Fisher statistic when appropriate.

A contrast of means will be applied to test the efficacy of the intervention in terms of the normality distribution of the variables. The results will be analyzed using the nonparametric Wilcoxon signed-rank test, which will allow us to check if there are differences between 2 populations from 2 dependent or related samples, or the Student *t* test for normally distributed samples. For independent samples, the nonparametric Mann-Whitney *U* test will be used.

The strength of the relationship between continuous data will be determined from the Pearson or Spearman correlation. The intraclass correlation coefficient will be used if it is necessary to measure concordance between measurements at different times of the study. To identify sociodemographic and clinical characterization variables (independent variables) related to the intervention and the different response variables (dependent variables), multivariate, linear, logistic, or Cox proportional analyses will be performed, as appropriate for each response variable.

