### Patient Selection

#### Setting

A total of 4 basic health areas located in the south of Spain, including 2 hospitals, will participate. The health care centers belonging to the clinical management units with the best mortality rates during hospital admission and at 30 days after discharge (12.7% and 14.3 %, respectively) and those with the highest rates (28% and 30.4%, respectively) were considered.

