#### Sample Size

The HL will be selected as the main outcome to evaluate the effectiveness. This outcome will be measured using the Spanish version of the 47-Item European Health Literacy Questionnaire (HLS-EU-Q47), which achieved a mean score of 32.88, over a possible range of 0 to 50 points, with an SD of 6.10 in the study setting [36]. An increase of at least 10% in the score will be considered clinically relevant due to the mHealth intervention. Accepting an α risk of .05 and a β risk of .90 in a bilateral contrast, 118 participants were needed in every group. A loss to follow-up rate of 30% was considered. However, the calculation is based on a minimum reference of sample observations, so an effort will be made to recruit as many participants as possible to increase the precision of the estimates.

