#### Description of the Intervention

The mHealth app aimed at empowering HL and self-management of the patients with multimorbidity with HF and complex health needs. It will be developed ad hoc based on the information obtained from the consensus sessions of experts (patients and professionals) and in accordance with the gamification methodology [39]. Although the final choice of the content will depend on the resulting decisions of the experts, it is intended to offer information and resources to the patient according to the level of HL identified and considering the main actions recommended to be incorporated to improve the overall health outcomes of these patients [12]. Thus, the participants in the experimental group will receive the mHealth app and will agree with the health care professional on 3 objectives related to the self-management of their disease, which they will have to achieve within a proposed period, being assisted by the mobile app, which will provide feedback and reinforcement in the achievement of these objectives. The stages and timing are described in Table 1. The intervention carried out in the control group participants will be based on usual clinical practice. Like the experimental group, they will agree with the health professional on 3 objectives they will have to achieve within the proposed time frame. This process (evaluation of the efficacy of the mHealth intervention with 2 groups) will last 12 months.

**Table 1 table1:** Stages of intervention.

Stage	Description	Timing (months)												
0	Detection of potential study participants. Presentation of the project and collection of informed consent.	✓^a^												
1	Baseline data collection for both groups.	✓												
2	For both groups, the patient and the practitioner will agree on the first health goal. On an individual basis, the nurse will present the main aspects related to the use and management of the app to the members of the expert group. The patient’s expectation of self-efficacy in using the app will be assessed to prevent adherence problems concerning the use of mobile health and difficulties in using the app (digital literacy) will be resolved.	✓	✓	✓										

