#### Randomization

Block randomization has been considered. The total number of participants will be divided by the number of study centers in equal parts. The number assigned will be for each center and will be considered a block in terms of randomization. An external collaborator (blinded) will use a computer-generated randomization list to assign patients to the groups such that, in each block (center), 50% of the patients will go to the control group (usual clinical practice) and 50% to the intervention group (usual clinical practice and mHealth app). This information will be available only to the principal investigator.

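### A within-arm before-after test is listed as a test of efficacy beside an unadjusted between-arm test, and the protocol does not say which decides

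*Protocol article*

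**What the plan says.** The efficacy paragraph of the Protocol article (Data Analysis: Data Encoding) opens with "A contrast of means will be applied to test the efficacy of the intervention in terms of the normality distribution of the variables". It goes on: "The results will be analyzed using the nonparametric Wilcoxon signed-rank test, which will allow us to check if there are differences between 2 populations". The rest of that sentence limits this test to paired samples and offers Student's t test where the data are normal. The next sentence begins "For independent samples, the nonparametric Mann-Whitney" and completes the U test. Normality is judged beforehand by Kolmogorov-Smirnov and Shapiro-Wilk tests.

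The paragraph does not say which test decides efficacy, or whether the between-arm test is applied to the final score or to the change. No covariate enters either test. The regression models named at the end of the section are for finding sociodemographic and clinical characteristics related to the responses. They are not described as the efficacy test, and they name neither baseline score nor centre.

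Four other places bear on this:

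- Sample Size: "The HL will be selected as the main outcome to evaluate the effectiveness", measured by the HLS-EU-Q47.
- Description of the Intervention, Table 1, stage 1: "Baseline data collection for both groups". The same section has control patients agree three objectives with the professional, as the app arm does.
- Randomization: "in each block (center), 50% of the patients will go to the control group".
- Setting: centres were drawn from units with the best mortality rates and from "those with the highest rates (28% and 30.4%, respectively) were considered".

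**The concern.** The trial is randomised in order to compare app with no app. A paired test within the app arm asks something else: whether those patients' scores moved over the intervention. They could move because of goal-setting, repeated checks, familiarity with the questionnaire or regression to the mean, and control patients are exposed to all of these too. With both kinds of test listed under efficacy and no order between them, a significant before-after change in the app arm could be reported as efficacy under the plan as written.

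The between-arm test has lesser faults. It is picked after looking at the data. It uses neither the baseline score, which is collected anyway, nor the centre, within which allocation is balanced. If Mann-Whitney is the test chosen, it does not itself yield a difference in points to set against the 10% relevance threshold in Sample Size.

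**Working it through.** **Inputs from the protocol (Sample Size).** The HLS-EU-Q47 "which achieved a mean score of 32.88", with SD 6.10. The relevant increase is 10%, so 0.10 × 32.88 = 3.288 points, read as a between-arm difference. Alpha is 0.05 two-sided, with 118 per group and 30% loss. The stated beta risk of 0.90 is read as 90% power.

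**The plan's own figure.** n = 2 × [6.10 × (1.960 + 1.282) / 3.288]² = 72.3, so 73 per arm, and 73 / 0.70 = 104.3, so 105 after loss. The stated 118 is not reproduced. That is a separate matter. Here 118 is taken as the number recruited, which leaves 118 × 0.70 = 82.6, about 83 completers per arm.

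**Assumptions not in the protocol.** These are the baseline-outcome correlation r, an equal improvement in both arms, and the share of variance lying between centres. Each is shown over a range.

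**1. The paired test when the app has no effect.** The SD of change is 6.10 × √[2(1 − r)], and the standard error is that divided by √83. The chance of significance comes from the noncentral t distribution with 82 degrees of freedom. The arms are independent, so the chance of significance in the app arm only is p(1 − p).

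| r | Improvement in both arms | SD of change | SE | p, app arm significant | p(1 − p), app arm only |
|---|---|---|---|---|---|
| 0.5 | 1.0 | 6.10 | 0.670 | 31% | 22% |
| 0.5 | 1.5 | 6.10 | 0.670 | 60% | 24% |
| 0.7 | 1.0 | 4.73 | 0.519 | 48% | 25% |
| 0.7 | 1.5 | 4.73 | 0.519 | 82% | 15% |

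A simulation with the signed-rank test itself (3,000 trials, 82 per arm, r = 0.5, normal scores) agrees. The app arm is significant in 31% of trials at 1.0 point and 59% at 1.5 points, and the app arm alone in 23% and 26%. With improvements from 0 to 3.288 points, Mann-Whitney and ANCOVA between arms rejected in 4.5% to 6.1% of the same trials.

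**2. Precision of the between-arm test at the target effect.** Baseline adjustment reduces the residual SD to 6.10 × √(1 − r²). Power is for 3.288 points with 83 per arm.

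| Analysis | Residual SD | SE of difference | Power |
|---|---|---|---|
| Unadjusted | 6.10 | 0.947 | 93% |
| Adjusted, r = 0.3 | 5.82 | 0.903 | 95% |
| Adjusted, r = 0.5 | 5.28 | 0.820 | 98% |
| Adjusted, r = 0.7 | 4.36 | 0.676 | 99.8% |

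**3. Centre.** If a share ρ of the variance lies between centres and allocation is balanced within them, ignoring centre overstates the standard error by a factor 1 / √(1 − ρ). This is 1.026 at ρ = 0.05 and 1.054 at ρ = 0.10, so about 3% to 5%.

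**The case against.** The strongest reply is that the trial's aim is plainly between-arm and a valid between-arm test is named. The Abstract's objective is set relative to routine practice, the Results section expects differences from the control group, and the Study Summary in the Discussion expects differences both after use and against control. That last statement may be why both kinds of test are listed. All of this stands. A reader might infer from the order of the sentences that the before-after test is the primary one and the between-arm test an afterthought. The protocol does not say so; it leaves the order open.

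The 31% to 82% also needs care. A reader might take it as the trial's false-positive rate. It would be that only for someone who looked at the app arm's paired test alone. If both arms improve, the control arm's paired test will often show it as well. The misleading pattern, significant in the app arm only, occurs in about 15% to 25% of trials, and the between-arm test holds near 5%.

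The lack of adjustment costs precision, not validity, and at the target effect the unadjusted test already exceeds the planned 90% power. The gain looks larger at half the target (1.64 points), where power rises from 41% to 51%, 58% or 68% at correlations of 0.5, 0.6 and 0.7. That effect lies below the protocol's own relevance threshold, so it is not the measure to judge by. The centre effect is small and errs on the cautious side, and nothing in the protocol shows that health literacy differs by centre. Planned descriptive statistics by group would also let scores in points be reported.

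Finally, a journal article may leave covariates to an analysis plan. Here, though, the article states the efficacy tests itself. A paired test offered for efficacy with nothing to say which test decides is a fault in what is written.

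**Conclusion.** The point holds as a should-fix. The main fault is that a within-arm test, which does not estimate the app effect, is listed as a test of efficacy on equal terms with the between-arm test. With no app effect and an assumed equal improvement of 1.0 to 1.5 points, it would be significant in the app arm in 31% to 82% of trials and in the app arm only in about 15% to 25%, for assumed correlations of 0.5 to 0.7 and 83 completers per arm.

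The lesser fault is lost efficiency in a valid test: 93% power at the target, against 95% to 99.8% with baseline adjustment, and a standard error about 3% to 5% too large if 5% to 10% of variance lies between centres. These gains rest on correlations and centre variance that the protocol does not give. The documents do not support saying that the between-arm comparison is missing, biased or underpowered for the stated target.

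**What to change.** In Data Analysis: Data Encoding, name one primary efficacy analysis: ANCOVA of the post-intervention HLS-EU-Q47 score on arm, baseline HLS-EU-Q47 and centre, reporting the adjusted difference in points with its 95% confidence interval. State that this comparison decides efficacy. Do not let a normality test choose the method; give a rank-based or bootstrap version as a sensitivity analysis. Report within-arm changes as description, without efficacy p-values.

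The cost is a change of wording before the data are unblinded. Baseline score and centre are already recorded, and SPSS, which the protocol names, fits the model.

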### Ethics and Dissemination

This study has been approved by the Cadiz Research Ethics Committee. The aim of the study and the anonymity of participants, as well as the voluntary nature of participation, will be explained before the participants start and their informed consent will be requested. The participants will also be informed that the data obtained would be used for research purposes only. Findings from this study will be disseminated through peer-reviewed scientific journals and at key national and international scientific events. The study was registered in ClinicalTrials.gov (trial registration number: NCT04725526) on January 26, 2021.

### Public/Patient Involvement Statement

Neither the patients nor the general public were involved in the design, or conduct, or reporting, or dissemination plans of the study.

## Results

The content validation to develop the mobile app was completed in 2021. To optimize material and human resources, the research team has been divided into 6 working subgroups that correspond to the main areas of action for patients with multimorbidity with HF: (1) physical exercise and cardiac rehabilitation, (2) nutrition, (3) medication and therapeutic adherence, (4) warning signs and symptoms, (5) self-care/self-management (which includes the elimination of toxic habits), and (6) emotional management.

Throughout the first year of the project, comprehensive/systematic bibliographic reviews of the scientific evidence on mHealth interventions (by the thematic areas described above) aimed at improving the evolution/care of patients with multimorbidity with HF have been carried out.

Individualized telephone interviews with patients were conducted to obtain information on their opinions, needs, and experiences about the disease management. This information has been incorporated into the objectives/contents of the mHealth app. Based on these data, an expert consensus (professionals and patients) has been conducted to establish the contents and structure of the mobile app to proceed with the content validation and its beta version.

The results of the primary and secondary variables recorded in the experimental group (health literacy, number of readmissions, self-management, therapeutic adherence, general satisfaction, and performance in activities of daily living) will improve and there will be significant differences with the control group. The findings will be disseminated to stakeholders using various methods, including peer-reviewed journals, academic conferences, and other verbal and digital communication channels. In relation to the patentability of project results, the resulting mHealth app will be registered as an intellectual property.

## Discussion

### Study Summary

To our knowledge, this is the first study to develop a protocol for a randomized controlled trial of an mHealth intervention to improve HL and self-management in patients with multimorbidity with HF and complex health needs that is based on patients’ perceived needs. The content of the intervention has already been validated.

We will investigate the efficacy, effectiveness, and usability of the proposed intervention in patients with multimorbidity and HF. The experimental group will use the app, hoping that the results of the primary and secondary variables recorded will improve and that significant differences will become evident after use and after comparison with the control group.

It is expected that the intervention developed will be effective and, therefore, improve the level of HL, self-management and therapeutic adherence, reduce the number of admissions per year due to decompensation, and that the incidence rates of HF mortality (adjusted for age, sex, and risk) or 30-day postdischarge mortality of the experimental group under study will be lower than that of the control group.

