### Evaluation of Effectiveness

#### Sample Characterization, Primary and Secondary Assessment Variables, and Data Source.

See summary in Tables 2 and 3.

**Table 2 table2:** Measurement, recording, and data source of variables of characterization.

Type of variable		Register rank/format	Measurement	Source of data

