**Of main response**				
	Health literacy	0/50	HLS-EU-Q47^a^ [36]	Registration
		1-5/indicator	NOC^b^ code: 2015 [29]	Nursing record
	Self-management	1-5/indicator	NOC codes: 3102; 1803; 1830 [9,40]	Nursing record
		12-60	European Heart Failure Self-Care Behavior Scale [41]	Nursing record
	Number of readmissions 1m;12m	0-99	Registration	Registration medical history

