**Secondary response**				
	Personal autonomy basic activities of daily living	0-100	Barthel Index [35]	Registration
	Personal autonomy instrumental activities of daily living	0-8	Lawton-Brody Index [42]	Registration
	Therapeutic adherence	0-4	Morisky-Green Adaptation Questionnaire [43] and Recipe XXI	Registration
	Vital forecast	0-30	PROFUND Index [44]	Registration
	Satisfaction with service	0-10	Satisfaction Scale	Nursing record
	Mobile health device satisfaction	1-5	Satisfaction Scale	Built-in mobile health device registration

^a^HLS-EU-Q47: 47-item European Health Literacy Questionnaire.

^b^NOC: Nursing Outcomes Classification.

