#### Security Variables

No adverse effects of patients’ exposure in the experimental group were considered, so no safety variables were included in the study.

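### Lower mortality is expected in the app arm, but no listed variable records death, and readmission counts carry no time at risk

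*Protocol article*

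**What the plan says.** In the protocol article, the Study Summary in the Discussion expects the app to lower heart failure mortality, adjusted for age, sex and risk, or predicts that "30-day postdischarge mortality of the experimental group under study will be lower than that of the control group".

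The section on assessment variables defines what is measured by pointing to the tables: "See summary in Tables 2 and 3". Table 2 holds sociodemographic and clinical characteristics. Table 3 lists the main and secondary responses. Among the main responses is "Number of readmissions 1m;12m", with a range of 0 to 99, taken from the medical history. The item nearest to mortality is the vital forecast by the PROFUND Index, a prognostic score.

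The Security Variables section states that no adverse effects were considered, "so no safety variables were included in the study".

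On analysis, the article says: "A contrast of means will be applied to test the efficacy of the intervention". It names the t test, the Wilcoxon signed-rank test and the Mann-Whitney test. Linear, logistic or Cox models are mentioned for relating participant characteristics to the intervention and the responses.

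**The concern.** The article predicts a result on an outcome that appears neither in its list of variables nor under safety. An expectation about mortality needs observed deaths, and none are planned to be collected.

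The gap also reaches a main response. A patient who dies stops accruing readmissions, and one who dies early at home can score 0, the most favourable value. A raw count over a nominal 12 months therefore mixes how often patients are readmitted with how long they live. Without a date of death the two cannot be separated. If the app improved survival, as the Discussion expects, part of that benefit would appear as extra readmissions. If survival were worse with the app, readmissions would look better than they are.

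**Working it through.** **Step 1: is death recorded anywhere?**
- Study Summary: lower mortality expected in the experimental group.
- Table 2: no vital status.
- Table 3, main responses: health literacy, self-management, readmissions. No death.
- Table 3, secondary responses: two autonomy scales, adherence, PROFUND, two satisfaction scales. PROFUND gives a forecast, not an observed death.
- Security Variables: none.
- Completion Criteria and Withdrawal: loss of contact is listed; death is not listed separately.

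So no planned variable yields a death count, a mortality rate or time at risk. Cox models are mentioned, but no time-to-event variable is listed.

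**Step 2: how far could readmission counts be shifted?** The article gives no figure for readmissions or mortality in this trial, so there is none to reproduce. Assumptions:
- The Introduction says half of hospitalised heart failure patients are readmitted within a year. As a constant Poisson rate this is λ = −ln(0.5) = 0.69 per person-year.
- For 12-month control mortality I borrow the 30-day postdischarge rates in the Setting section as a range: 14.3% and 30.4%, from "12.7% and 14.3 %, respectively" and "28% and 30.4%, respectively". They are not trial estimates.
- Mortality with the app is assumed 30% lower (14.3% × 0.7 = 10.0%; 30.4% × 0.7 = 21.3%) or 50% lower (30.4% × 0.5 = 15.2%).
- With a constant hazard, mean time alive over the year is T(m) = m / [−ln(1 − m)]. The expected count is λ × T(m).

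Example: T(0.304) = 0.304 / 0.362 = 0.839 and T(0.152) = 0.152 / 0.165 = 0.922. The ratio is 0.922 / 0.839 = 1.10.

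| 12-month mortality, control v app | Mean years alive | Mean count, no true effect | Count ratio, app/control | True rate ratio 0.80 appears as |
|---|---|---|---|---|
| 30% v 30% | 0.841 v 0.841 | 0.583 v 0.583 | 1.00 | 0.80 |
| 14.3% v 10.0% | 0.927 v 0.949 | 0.642 v 0.658 | 1.02 | 0.82 |
| 30.4% v 21.3% | 0.839 v 0.889 | 0.581 v 0.616 | 1.06 | 0.85 |
| 30.4% v 15.2% | 0.839 v 0.922 | 0.581 v 0.639 | 1.10 | 0.88 |

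λ cancels in the ratio, so the ratios rest on the assumed mortality and constant hazards, not on 0.69.

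**Step 3: could 118 per group test mortality if deaths were recorded?** The 118 is the article's sample size for health literacy, taken here as stated. For two proportions, two-sided α = 0.05:

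power = Φ{ [ |p₁ − p₂|√n − 1.96√(2p̄(1 − p̄)) ] / √(p₁(1 − p₁) + p₂(1 − p₂)) }

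With p₁ = 0.304, p₂ = 0.2128 and n = 118: (0.0912 × 10.863 − 1.213) / 0.616 = −0.36, so power is 0.36. With p₁ = 0.127 and a 30% reduction, power is 0.15. Across control rates of 12.7% to 30.4%, power is 15% to 36% for a 30% relative reduction and 38% to 80% for a 50% reduction. At 90% power, a 30% reduction would need 483 to 1393 per group.

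**The case against.** The mortality sentence is an expectation in the Discussion. Mortality is absent from the objective, the aims, the sample size and the Results section's own list of variables expected to improve. It is not an endpoint, and deleting one sentence would remove the contradiction. This is fair, and it limits the weight of the point. Deletion would not, however, give the readmission comparison a time at risk.

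A second objection is that the article condenses a fuller protocol, and that handling of death and the choice of count model belong in an analysis plan. That stands for the model. It does not stand for the variable list: the article sets out what is recorded, excludes safety variables explicitly, and then predicts a result outside both. Deaths could be retrieved from the medical history, but the article does not plan it.

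A third is that the Setting rates describe units during admission and 30 days after discharge. Participants must have NYHA grade II disease in clinical stability, own a compatible device, and be free of persistent cognitive impairment and severe dependence. That stands. A reader might infer from those rates that death will be common in this sample, but the article does not show it. The Introduction's 50% mortality at 5 years is about 12.9% a year under a constant hazard (1 − 0.5^(1/5)), near the low end of the range used here.

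A reader might also infer that any harm would go unseen. That goes too far, because an excess of admissions would appear in the readmission counts. What would not be seen is an imbalance in deaths.

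**Conclusion.** The mismatch is documentary and needs no assumption: a mortality benefit is expected, yet nothing listed records death.

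The readmission part is conditional. A reader might infer that raw counts mislead whatever happens to survival. They do not: with equal mortality the count ratio stays at 1.00. If mortality falls with the app, the shift against it is about 2% to 10% under the assumptions shown, and a true rate ratio of 0.80 would appear as 0.82 to 0.88.

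Nor do the documents support a claim of serious false-positive inflation. In simulations with 1 readmission per year while alive, gamma-Poisson dispersion 1 and 118 per arm, the Mann-Whitney test rejects in about 5% of trials with equal mortality and about 6% at 30% v 20%. It reaches about 10% only at 30% v 10%, an extreme contrast.

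Recording deaths would make an imbalance visible but would not give a confirmatory mortality test at this size. Mortality within 30 days of discharge is also defined only for patients admitted after randomisation, so it does not compare the full randomised groups. The change is worth making but does not touch health literacy, the outcome on which the trial was sized.

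**What to change.** 1. Add all-cause death, with date, to Table 3. Take it from the medical history for every randomised patient, including those withdrawn, unless the patient refuses use of records.
2. Report deaths by arm descriptively, counted from randomisation, without presenting the comparison as a powered test.
3. Analyse 12-month readmissions as a rate with log time at risk as offset, for example by negative binomial regression. Add death or readmission as a companion analysis.
4. If deaths are not to be recorded, remove or reword the mortality expectation in the Study Summary.

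The cost is one extra record field, from a source already used for readmissions, and slightly more analysis. Sample size and visits do not change.
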